## Methods

### Trial design

A closed cohort stepped wedge cluster randomized controlled trial (SWT) design will be applied. Figure 2 schematically represents this design. Within a time period of 30 months, the *ItFits-toolkit* will be rolled out sequentially to twelve implementation sites (clusters). The twelve clusters are randomly allocated to six sequences (A–F) defining the different time points at which the clusters will cross over from the control condition (*implementation-as-usual*) to the experimental condition (*ItFits-toolkit*). As such, each cluster acts as both the control and experimental group over time. The successive cross-over points are scheduled every 3 months. The *ItFits-toolkit* will be used by each cluster for a minimum of 6 months (*b* = minimal exposure period). During the 6-month exposure time, sites will receive technical support. The cohort will be encouraged to continue using the *ItFits-toolkit* after the minimal exposure period. Due to a potential intervention lag effect, it is expected that changes in the outcome measures become gradually visible in the data within and after the 6-month exposure period. As such, the effect is hypothesized to increase from no effect in the control condition (0) to a partial effect during the compulsory exposure period (½) to a full and lasting effect after the 6-month exposure (1). Data will be collected 3-monthly (T0–T9) to strike a balance between the ability of the measurements capturing change over time and the measurement burden. A pre-rollout period of 6 months is chosen to obtain stable measures of implementation-as-usual activities in all clusters. That means the first three measurements (T0–T2) consist solely of *implementation-as-usual* data and at T2 the first two clusters cross over to the experimental condition, followed by two clusters every 3 months.

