### Sample size and power estimates

This study has a fixed cluster sample size by design (*n* = 12 implementation sites) based on availability and willingness of organizations engaged in implementation of iCBT services to conform to the study’s eligibility criteria. For the staff-level outcome, a series of simulation studies was conducted using a multi-level degree of normalization data (i.e. NoMAD items) to estimate the minimal required number of staff members to sufficiently power the analysis. Here, a 5% increase in absolute normalization scores and an increased 3-month growth rate from .05 to .10 are assumed to be statistically decisive in superiority for either condition. The cluster sample size of 12 clusters, with 15 staff participants per implementation site per measurement wave, achieves > 80% power to detect this effect, using a two-sided test with a significance level *α* of .05. Taking a conservative study drop-out of 20% into account, the minimum staff sample size was set to *n* = 19 per implementation site. In line with the closed cohort design, each participant will be measured continuously over a period of 10 measurement waves. For all 12 clusters, this results in a total minimum sample size of 228 staff participants with 2280 repeated data points.

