### Statistical methods

For the normalization outcomes, a three-level GLMM will be conducted, with ‘Wave’ clustered at the ‘Staff’ level, and ‘Staff’ clustered at the ‘Site’ level, accounting for the correlation structure in the outcome. Random effects will be used to assess correlations between observations within and across units in the same clusters. Each regression parameter, including the intercept, will be allowed to vary within cluster levels ‘Staff’ and ‘Site’. Efficiency of the implementation process (i.e. normalization and service uptake divided by implementation costs) will be included in the separate analyses.

It will be tested whether the introduction of the *ItFits-toolkit* influences iCBT service uptake by patients across and within sites [55, 56]. An effect of the toolkit is demonstrated when service uptake shows a significant main effect of *ItFits-toolkit* use or an interaction effect of *ItFits-toolkit* use and measurement wave (time). Consequently, trial data will be analysed using generalized linear mixed modelling (GLMM) [55] with service uptake as the dependent variable, and measurement wave (time), *ItFits-toolkit* use (yes/no), and interaction between time and *ItFits-toolkit* use as independent variables. To account for the expected intervention lag effect, a fractional term for the ‘*ItFits*’ parameter will be included in the 6-month minimal exposure time (ranging from 0 to 1, i.e. 0–½–1). Service uptake outcomes will be modelled in a two-level GLMM, since these measures are collected at the site level only. Thus, to account for the correlation structure of the uptake outcome, ‘Wave’ is modelled to be clustered at the ‘Site’ level. All regression parameters will be allowed to vary.

For exploratory purposes, measures of exposure to the *ItFits-toolkit* (event-based log files showing intensity of use and level of continuous use), CSQ, SUS, and ORIC questionnaire data will be added as additional predictors of outcome in the above-described regression models.

In the analyses, all observed data will be included following the intention-to-treat principle. The ability of mixed models to estimate model parameters in the presence of missing observations will be used, and increased uncertainty caused by missing values will be accepted as a given quality of the results.

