The ImpleMentAll project applies a stepped wedge cluster randomized controlled trial design to determine the effectiveness of the *ItFits-toolkit*. Reasons for choosing the SWT design include practical feasibility and flexibility, fairness, and strength of the evidence [56]. A classical randomized controlled trial would not have been feasible due to the highly heterogeneous and reasonably small sample of organizations included in the study. It would not have been possible to alternatively randomize participants at individual level as this would have conflicted the naturalistic setting of the study. Due to repeated measures, a SWT requires less participants to adequately power the statistical analysis. However, achieving and maintaining a stable sample for the duration of the study will be challenging. Biases due to time trends such as organizational restructuring, data regulation policies and legislation, and technological advances need to be considered given the potential large intervention lag effect in implementation trials. A SWT design allows for the possibility to adjust for time trends in outcomes. It distributes the chances of such time trends affecting the dependent variables equally across the participating sites. Furthermore, the design increases practical feasibility of the study as it allows for sequential, batch-wise training of the implementation sites to the *ItFits-toolkit* and keeps guidance limited to those groups who are in the exposure condition.

The use of such a trial design is novel, but the literature in the field is growing at the time of writing. Generic guidance [33, 62] on how to conduct a SWT is available. However, there is no scientific literature on particular components of the design applied to implementation research, most notably the minimal exposure time to exert an effect in relation to the potential intervention lag effect. A minimal exposure period of 6 months was chosen as it strikes a reasonable balance between time constraints of the total trial period and to constitute to meaningful exposure by finishing one complete cycle of the *ItFits-toolkit*. Carry-over effects might occur when implementation sites cross over from the control to the experimental condition. The process evaluation conducted within this project is expected to shed light on the implementation mechanisms considering potential carry-over effects. This will be regarded when interpreting the results of the effectiveness study.

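### The toolkit is interacted with calendar wave, so the separately tested main effect refers to T0, when no site is exposed, and can be negative under a real benefit

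*Protocol article*

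**What the plan says.** The Statistical methods section writes the model out for service uptake. The predictors are measurement wave, toolkit use (yes/no) "and interaction between time and *ItFits-toolkit* use as independent variables". The success rule follows from these terms: "An effect of the toolkit is demonstrated when service uptake shows a significant main effect of *ItFits-toolkit* use or an interaction effect" with measurement wave. It names no direction and no wave at which the main effect is to be read. To allow for lag, "a fractional term for the ‘*ItFits*’ parameter will be included in the 6-month minimal exposure time (ranging from 0 to 1, i.e. 0–½–1". Once the 6 months are over, that term stays at 1.

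The paragraph on normalization (NoMAD, the primary outcome) gives the levels and random effects but no separate list of fixed effects.

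Under Trial design, "the first three measurements (T0–T2) consist solely of *implementation-as-usual* data". Two sites cross over at T2 and two more every 3 months after that, so the last pair crosses at T7. Under Sample size and power estimates, the planning effect for normalization is a 5% rise in level, and "an increased 3-month growth rate from .05 to .10 are assumed to be statistically decisive". The Discussion adds: "A SWT design allows for the possibility to adjust for time trends in outcomes".

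**The concern.** In a model with wave, toolkit and toolkit by wave, the toolkit coefficient is the effect where wave equals zero. On the protocol's own numbering that is T0, inside the period with control data only. The interaction lets the effect depend on the calendar date, whereas a change in growth caused by the toolkit would depend on how long a site has used it. In a stepped wedge the two differ by site: at T8 a site that crossed at T2 has six waves of use and a site that crossed at T7 has one.

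This matters because each coefficient is its own route to success. A significant negative T0 coefficient would satisfy the rule as written, and the interaction would understate the growth change. If wave enters as a straight line, a curved secular trend can also pass into both toolkit terms.

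**Working it through.** **Inputs from the protocol.** 12 sites, six sequences of two; waves T0 to T9; crossovers at T2, T3, T4, T5, T6 and T7; growth 0.05 rising to 0.10 per wave; toolkit coded 0, ½, 1. Exposed sites at T0 to T9 are 0, 0, 0, 2, 4, 6, 8, 10, 12, 12.

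**The plan's own figure.** 15/(1 - 0.20) = 18.75, rounded up to 19; 19 × 12 = 228; 228 × 10 = 2280. These reproduce. The power above 80% comes from simulations whose variance components are not in the article, so it cannot be reproduced.

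**Assumptions.** Growth changes at each site's crossover. Wave is coded 0 to 9. The level step is 0, 0.05 or 0.175, because the article does not give the 5% in scale points. Outcomes are on an identity scale. Site-mean ICC is 0.5 to 0.95 with a random site intercept; a wider set of 72 variance combinations adds random slopes and random toolkit effects.

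**Why the sign can turn.** With no step, a site crossing at wave c has a true effect of 0.05 × (t - c) at wave t.
- Within one site this equals -0.05c + 0.05t. In the protocol's terms the main effect is -0.05c, from -0.10 (c = 2) to -0.35 (c = 7), and the interaction is 0.05.
- Across exposed sites at one wave (T3 to T8), mean time since crossover is (t - 1)/2, so the mean effect is 0.025 × (t - 1). That line has slope 0.025 and reaches -0.025 at T0.

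The mixed model blends the two, although the true effect is at least 0.05 at every exposed observation and averages +0.154.

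**Projection.** Generalized least squares on noise-free site means, toolkit = ½ at 3 months and 1 from 6 months unless stated.

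| Truth | Main effect (T0), random intercept | Main effect, 72 combinations |
|---|---|---|
| Growth only, linear wave | -0.09 to -0.08 | -0.168 to -0.071 |
| Growth only, categorical wave | -0.17 to -0.15 | -0.167 to -0.044 |
| Plus 0.05 step following the fraction, linear | -0.04 to -0.03 | -0.118 to -0.021 |
| Same, categorical | -0.12 to -0.10 | -0.117 to +0.006 (93% negative) |
| Plus immediate 0.05 step, linear | -0.02 to -0.01 | -0.090 to 0.000 |
| Same, categorical | -0.05 to -0.04 | -0.052 to +0.072 (33% negative) |
| Plus 0.175 step following the fraction, either | +0.01 to +0.10 | +0.007 to +0.131 |

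With growth only, the interaction is about 0.03 (linear wave) to 0.045 (categorical) under a random intercept, against a planned 0.05; the wider set goes down to 0.017. If ½ also applies at the 6-month wave, growth only stays negative throughout, a 0.05 step following the fraction gives 75% to 96% negative, and an immediate 0.05 step gives none.

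**Precision.** With linear wave, adding the interaction multiplies the main effect's SE by 1.9 to 2.07. A constant effect with 80% power has a standardized size of 1.960 + 0.842 = 2.802. Then Φ(2.802/1.90 - 1.960) = 0.31 and Φ(2.802/2.07 - 1.960) = 0.27.

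**Secular trend.** Take no toolkit effect and an assumed rise of 0.45 (9 × 0.05) that levels off at T4. With linear wave the fitted main effect is +0.36 to +0.39 and the interaction about -0.08. With categorical wave both are zero.

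**After the change.** With waves since crossover in place of toolkit by wave, the fit returns the planned level and the 0.05 growth change exactly when there is no step or the step follows the fraction. With an immediate full step and fractional coding it returns a level of +0.055 to +0.073 and growth of +0.041 to +0.047.

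**The case against.** Several objections have force.

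- **Two outcomes.** The terms and the success rule are written for uptake, which is exploratory; the planning effect belongs to normalization. A reader might infer that the primary analysis is certainly affected. The documents do not say so. The carry-over is likely only because no other fixed effects are given for NoMAD.
- **When growth starts.** The sample-size section does not say that faster growth counts from crossover. If it is read on calendar time, the model is correct and nothing reverses. But a growth effect of 0.05 × wave would then give a T7 site 0.40 at its first exposed wave (T8) and a T2 site 0.15 at its own (T3), before the ½ weight. Nothing in the protocol suggests that.
- **The fraction.** The 0, ½, 1 term is an element of time since crossover, and Trial design describes a full, lasting effect after 6 months. This narrows the problem. It does not remove it, because the term carries no growth beyond 6 months.
- **A negative T0 coefficient is not a harmful toolkit.** A reader might infer that the model would report harm or miss the benefit. It need not: the fitted effect averaged over exposed observations is positive in every variant, and so is the effect at mid-trial (wave 4.5).
- **Coding detail.** Centring, and linear or categorical wave, may be settled in an analysis plan. That is fair, and the secular-trend result depends on linear wave. Centring would repair the main effect's sign but not the interaction's meaning.

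**Conclusion.** The point stands in limited form. For uptake, the protocol fixes a calendar-wave interaction and an undirected either/or rule whose main effect, on T0 to T9 numbering without centring, describes a wave with no exposed site. That is algebra and holds on any link scale. For NoMAD it applies if the same terms are used.

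The sizes are conditional. If growth changes at crossover, the main effect is about -0.08 to -0.17 with no step and generally still negative with a 0.05 step; an immediate step or a longer ½ period can remove the reversal. With a 0.175 step it is positive under the protocol's fraction. The interaction recovers about 0.03 to 0.045 of 0.05, and in a linear-wave model it roughly doubles the main effect's SE. The documents do not support saying that the sign always reverses, that the overall toolkit effect is estimated with the wrong sign, or that the stated power is wrong. Leakage of a plateauing trend holds only if wave is linear.

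**What to change.** In the uptake model, and in the NoMAD model if it uses the same terms:

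1. Enter wave as a categorical fixed effect.
2. Keep the 0, ½, 1 toolkit term.
3. Replace toolkit by wave with the number of waves since the site's scheduled crossover.
4. Replace the either/or rule with one pre-specified contrast, the average toolkit effect over exposed waves, with the direction of benefit stated.
5. For NoMAD, match the power statement to that contrast, and say from when the faster growth counts.

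Steps 1 and 3 belong together: categorical wave with toolkit by wave retained has a main-effect SE about 3.3 to 3.9 times that of the categorical model without the interaction.

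Data collection and the schedule do not change, but there is a cost in precision. Under an assumed site ICC of 0.5 to 0.95, the SE of the contrast is about 13% to 16% above the same model with linear wave. It is about 8% to 37% above a constant-effect linear-wave model, the low end with the fraction and the high end with 0/1 coding. As a guide, a contrast with exactly 80% power under linear wave would have Φ(2.802/1.13 - 1.960) = 0.70 to Φ(2.802/1.16 - 1.960) = 0.68. The power may therefore be less favourable than stated and should be re-simulated with the sponsor's own variance components.

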### Process evaluation

#### Implementation-as-usual

The *implementation-as-usual* process evaluation will explore *implementation-as-usual* activities in which implementation sites were engaged in prior to receiving the *ItFits-toolkit*. This analysis will identify and describe these implementation actions and determinants they focused on.

#### The *ItFits-toolkit*

A qualitative process evaluation will be conducted to study how the effects of the *ItFits-toolkit* were achieved and to obtain a better understanding of the underlying theoretical and conceptual mechanisms of tailored implementation. The process evaluation will focus on (1) understanding what implementers do with the *ItFits-toolkit*, (2) understanding and describing how the *ItFits-toolkit* gets reconfigured and adapted within and across settings when it is used, and (3) identifying, describing, and understanding the micro-, meso-, and macro-mechanisms that shape *ItFits-toolkit* use within and between implementation sites. The *ItFits-toolkit* process evaluation will be theoretically informed by Normalization Process Theory (NPT) [35], Self-determination Theory (SDT) [57], and work within organization studies, especially on organizational routines [58, 59]. The conceptual ideas within these bodies of literature will enable the research team to focus on the work through which the *ItFits-toolkit* is implemented, what motivates individuals to work with the *ItFits-toolkit*, and how the *ItFits-toolkit* facilitates the structuring of time, resources, and people to support implementation. Four qualitative research methods will be used within the process evaluation, including theory-informed interviews with Implementation Leads and main informants (e.g. implementation practitioners and trainers of the *ItFits-toolkit*), in situ and distal observations of implementers engaged with the *ItFits-toolkit*, process data from the use of the *ItFits-toolkit*, and analysis of documents, texts, and technological specifications produced and made available by *ItFits-toolkit* users. Interviews with the Implementation Leads will be generally conducted in English. More focused qualitative observations will be conducted in some purposively sampled sites according to the spoken languages of the researchers. This work will involve in situ and distil observations of meetings of the core implementation teams and meetings with key stakeholders. Qualitative data will be analysed according to the analytical framework developed and will be conducted according to the standard procedures of rigorous qualitative analysis [60]. Analysis will occur concurrently with data collection following the stepped order of implementation sites’ entry into the trial. This allows for emerging trends found in earlier rounds of fieldwork to be explored in subsequent ones. All data will be audio-recorded, transcribed verbatim, and analysed using framework analysis [61]. The results of the *ItFits-toolkit* process evaluation will be used to further inform the outcome evaluation.

## Discussion

The ImpleMentAll study is a large-scale international collaborative research project designed to study the effectiveness of tailored implementation and better understand the mechanisms of implementing iCBT for common mental disorders. A newly developed digitally accessible toolkit by which implementation strategies are prospectively developed, adapted, applied, and evaluated will be tested for its effectiveness compared to usual implementation activities. The toolkit will be introduced in twelve different mental health care organizations in nine countries across Europe and Australia. This real-world research setting provides a variety in health care systems, iCBT services, policies, implementation climate, and levels of experience in delivering iCBT. Tailored implementation is thought to be generically applicable across care contexts. The conceptual idea behind the tailoring process builds on recent literature findings and methods in the field of implementation (publication forthcoming).

The ImpleMentAll project applies a stepped wedge cluster randomized controlled trial design to determine the effectiveness of the *ItFits-toolkit*. Reasons for choosing the SWT design include practical feasibility and flexibility, fairness, and strength of the evidence [56]. A classical randomized controlled trial would not have been feasible due to the highly heterogeneous and reasonably small sample of organizations included in the study. It would not have been possible to alternatively randomize participants at individual level as this would have conflicted the naturalistic setting of the study. Due to repeated measures, a SWT requires less participants to adequately power the statistical analysis. However, achieving and maintaining a stable sample for the duration of the study will be challenging. Biases due to time trends such as organizational restructuring, data regulation policies and legislation, and technological advances need to be considered given the potential large intervention lag effect in implementation trials. A SWT design allows for the possibility to adjust for time trends in outcomes. It distributes the chances of such time trends affecting the dependent variables equally across the participating sites. Furthermore, the design increases practical feasibility of the study as it allows for sequential, batch-wise training of the implementation sites to the *ItFits-toolkit* and keeps guidance limited to those groups who are in the exposure condition.

The use of such a trial design is novel, but the literature in the field is growing at the time of writing. Generic guidance [33, 62] on how to conduct a SWT is available. However, there is no scientific literature on particular components of the design applied to implementation research, most notably the minimal exposure time to exert an effect in relation to the potential intervention lag effect. A minimal exposure period of 6 months was chosen as it strikes a reasonable balance between time constraints of the total trial period and to constitute to meaningful exposure by finishing one complete cycle of the *ItFits-toolkit*. Carry-over effects might occur when implementation sites cross over from the control to the experimental condition. The process evaluation conducted within this project is expected to shed light on the implementation mechanisms considering potential carry-over effects. This will be regarded when interpreting the results of the effectiveness study.

The ImpleMentAll study does not include an evaluation of the clinical effectiveness of the iCBT services per se, as the focus lies on establishing the effectiveness of the *ItFits-toolkit*—the implementation intervention*.* The effectiveness of the *ItFits-toolkit* will be investigated by measuring implementation outcomes mainly on organization and staff level, anticipating that change processes to successfully implement iCBT in routine care are predominantly taking place at those levels. The perspective of the patient using the iCBT services will be considered indirectly by assessing the completion rates of the services by the patients. This means that the implementation could be perceived as successful from the perspective of the organization and staff, irrespective of improvements in clinical outcomes (e.g. symptom reduction) in the patient.

The field of implementation research is still young, and therefore, access to thoroughly validated and theory-based measurement instruments is limited [63, 64]. The measurement instruments used to assess implementation success or related outcomes (i.e. NoMAD, ORIC, and implementation costs measure) are relatively new, though promising [42–44, 51]. Experience of the field to use these validated measures is low, and therefore, the interpretation might not be as straightforward compared to well-established instruments. Uncertainties around sensitivity to change in these instruments are present, and further psychometric validation is planned.

The ImpleMentAll study engages in a number of challenges, mostly related to the relatively new concepts under study, the fast-changing world of technology-assisted interventions, and the complex and heterogenous implementation contexts. In that sense, the ImpleMentAll study is well-positioned to take the first step towards exploring the effectiveness of an online self-help toolkit for a tailored implementation supporting the implementation of evidence-based eHealth in mental health care. As such, it will contribute to implementation science by investigating the effectiveness of tailored implementation and providing a better understanding of the process and methods for tailoring implementation strategies. Measurement instruments for implementation outcomes related to implementation success will be further improved and validated. If effective, the *ItFits-toolkit* will be made available to implementers supporting them in identifying barriers, selecting, localizing, and applying appropriate implementation strategies for successfully implementing iCBT in their practices. This will ultimately be beneficial for the large proportion of individuals in need of evidence-based health care.

